Our transdisciplinary team of researchers, practitioners, and community partners has collaborated for the past 7-years to effectively address diabetes prevention challenges through the development, testing, refinement, and expansion of a culturally-grounded lifestyle intervention for obese Latino youth with prediabetes, which if efficacious, could be taken to scale. The overall approach applies an adapted Ecodevelopmental framework to leverage community, family, peer, and individual-level influences during the critical transition period of adolescence when changes in health behaviors and health outcomes are linked to future health trajectories. The intervention draws upon Social Cognitive Theory and employs key behavioral modification strategies from the DPP to enhance self-efficacy and foster social support for making healthy behavior changes. *Promotores* (community health workers) deliver nutrition education to families to facilitate dietary changes while group exercise classes for youth are led by YMCA staff to increase physical activity levels. Feasibility and initial efficacy for improving glucose tolerance and increasing insulin sensitivity was established through a pilot study. The pilot intervention also led to significant improvements in QoL, eating behaviors, fitness, and multiple cardiovascular disease risk factors without weight loss. We are currently conducting an RCT that expands upon the pilot to rigorously evaluate intervention effects in obese Latino adolescents. To date, we have enrolled 160 obese youth and the rate of prediabetes in this community sample is ~15%. Preliminary analyses on prediabetic youth show robust and sustained improvements on targeted outcomes including glucose tolerance, insulin sensitivity, and QoL. For ethical reasons, we do not randomize prediabetic youth to the control condition in that study. We now propose to build upon these compelling preliminary findings and further refine our culturally-grounded lifestyle intervention to test the efficacy, as compared to usual care, for improving health and QoL by **preventing T2D in obese Latino adolescents with prediabetes**.

**Specific Aim 1:** Test the short-term (6-month) and long-term (12-month) efficacy of this culturally-grounded, community-based lifestyle intervention as compared with a usual care control group for improving glucose tolerance and increasing insulin sensitivity in 120 obese Latino adolescents age 12-16 with prediabetes.

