## BIOSCIENCE INSTRUCTIONS AND TEMPLATE

NUMBER

HRP-503b

DATE

3/22/2022

PAGE

11 of 13

**Specific Aim 1:** We will test the hypothesis that adolescents who complete the intervention will exhibit significantly greater short-term and long-term improvements in glucose tolerance and increases in insulin sensitivity compared to UCC. ANCOVA models will use pretest measures as a covariate and the experimental groups (i.e., intervention vs. UCC) for comparisons. Separate analyses will be conducted for 6- and 12-months. We will explore interactions between the covariate (baseline measure) and group to determine whether adolescents with lower baseline scores differentially benefit from the program. Assuming no interaction is found, we will examine the main effect of group assignment on the outcome measure after adjusting for baseline. We will also conduct repeated measures ANCOVA models to examine differences in the effect of the intervention on primary outcomes between 6- and 12-month time points.

**Specific Aim 2:** We will use the same ANCOVA models described above to examine the effects of the intervention on general and weight-specific QoL. Results will indicate whether adolescents who were randomized to the intervention report greater increases in QoL compared to adolescents randomized to UCC.

**Specific Aim 3:** We will explore the mediating effects of changes in total body composition on changes in T2D risk markers by path analysis. Each mediation model will include three variables: (1) experimental group membership represented by dummy codes, (2) a mediator measure (e.g., fat mass), and (3) an outcome measure. The model specifies direct paths from group membership to the mediator and outcome. Path coefficients and standard errors for these paths will be estimated. Effect size measures will include: (1) direct effects on outcome and (2) mediated or indirect effects on outcome. The latter will be estimated using path coefficient estimates with standard errors.

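### The Aim 3 mediation model has no baseline covariates and does not write down the mediator-to-outcome path, so its indirect effect is open to bias that data already collected could remove

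*Supplement*

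**What the plan says.** The Aim 3 text is in the Supplement, Section 16 (Data Management and Confidentiality).

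- **Purpose:** "We will explore the mediating effects of changes in total body composition on changes in T2D risk markers by path analysis".
- **Size of the model:** "Each mediation model will include three variables". These are group membership, the mediator (fat mass is the example) and the outcome. No baseline covariate is listed.
- **Paths:** "The model specifies direct paths from group membership to the mediator and outcome". Coefficients and standard errors are then promised for the paths just named.
- **Reported quantities:** "Effect size measures will include: (1) direct effects on outcome and (2) mediated or indirect effects on outcome". On the indirect effect: "The latter will be estimated using path coefficient estimates with standard errors".
- **Contrast with Aims 1 and 2, same section:** "ANCOVA models will use pretest measures as a covariate". Aim 2 uses the same models.

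The Aim 3 text does not say which visits supply the mediator and the outcome, whether they enter as follow-up values or as changes, or which test or interval is used for the indirect effect. Section 8 schedules DXA at baseline, 6 and 12 months, and Aim 1 assesses glucose tolerance and insulin sensitivity at 6 and 12 months against baseline.

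**The concern.** An indirect effect is the product of two coefficients: group to mediator (a), and mediator to outcome given group (b). Both paths that the plan names start at group, so b is not written down. If only those two paths were fitted, the group-to-outcome coefficient would be the total effect, not the direct effect that the plan wants to report.

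The more substantive gap is baseline. Randomisation makes the arms comparable, so a is protected. Nobody is randomised to a level of fat mass, so b is an observational association. A participant with more fat mass and higher glucose at entry will tend to have more of both later, and a model without the baseline values counts that persistence as an effect of fat mass on glucose.

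At stake is how Aim 3 is read. Section 2 argues that body composition may matter more than weight loss for preventing diabetes in these adolescents. Positive correlation at baseline could produce apparent support for that argument where there is none.

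**Working it through.** **The plan's own figures.** The plan gives no effect size, SD, power or allocation ratio, and no figure for Aim 3. Its N of 120 (Sections 2 and 5) is a screening yield: 300 × 0.40 = 120. Everything below apart from N rests on assumed values.

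**1. What the two written paths deliver.** Total effect = direct effect + a×b. Take direct effect = 0, a = 0.5, b = 0.3. The total is 0 + 0.5 × 0.3 = 0.15. A large simulated sample (n = 400,000) gave a group-to-outcome coefficient of about 0.15, where the true direct effect was 0. The mediator-to-outcome path is needed to separate the two.

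**2. Bias when b is added but the baselines are not.** Assumptions: baseline mediator and outcome have unit SD and correlation r; each follow-up value has correlation s (stability) with its own baseline; a = 0.5 SD; true b = 0. Within arm:

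- Follow-up values: covariance of mediator and outcome = s²r and mediator variance = 1, so the spurious a×b = 0.5·s²·r.
- Change scores: covariance = (1−s)²r and mediator variance = 2(1−s), so the spurious a×b = 0.5·(1−s)·r/2.

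| r | s | Follow-up: formula (simulated) | Change: formula (simulated) | Both baselines adjusted (simulated) |
|---|---|---|---|---|
| 0.2 | 0.5 | 0.025 (0.026) | 0.025 (0.026) | 0.001 |
| 0.2 | 0.8 | 0.064 (0.063) | 0.010 (0.011) | 0.000 |
| 0.4 | 0.5 | 0.050 (0.050) | 0.050 (0.051) | 0.001 |
| 0.4 | 0.8 | 0.128 (0.129) | 0.020 (0.021) | 0.001 |

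The bias is proportional to a, so it vanishes if the intervention does not move the mediator.

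With a true indirect effect of 0.15 (b = 0.3) and r from 0 to 0.4, the unadjusted estimates ran from 0.054 to 0.183 on follow-up values and from 0.112 to 0.161 on change scores. The adjusted model gave 0.148 to 0.152. The error can therefore go either way when there is real mediation.

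**3. Choice of interval, if a normal-theory test is meant.** N = 120, 1:1, unit residual SDs, no direct effect, two-sided 5%, 2,000 simulated trials per setting. The comparison is the delta-method (Sobel) z test against a Monte Carlo interval from the distribution of the product.

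| a | b | Normal-theory | Product interval |
|---|---|---|---|
| 0.3 | 0.3 | 0.19 | 0.34 |
| 0.4 | 0.3 | 0.34 | 0.52 |
| 0.5 | 0.3 | 0.50 | 0.69 |
| 0.5 | 0.4 | 0.67 | 0.77 |
| 0.8 | 0.39 | 0.95 | 0.98 |

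With exactly one path at zero, the rejection rate was 0.009 to 0.016 for the normal-theory test and 0.041 to 0.045 for the product interval, against a nominal 0.05. With an assumed 20% loss (120 × 0.8 = 96), the a = 0.5, b = 0.3 row becomes 0.34 against 0.54. A bootstrap interval was not simulated.

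**The case against.** The case for leaving the text alone is fair in several respects.

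- **The indirect effect is promised.** A reader might infer from the listed paths that it will never be estimated. The documents do not support that. The sentences that follow commit to both direct and indirect effects, and a three-variable path analysis with a named mediator implies the missing path. What stands is an incomplete specification.
- **No test is named.** A reader might infer that a conservative normal-theory test is planned. The text says only that path coefficients and their standard errors will be used, and those are also the inputs to a product-distribution interval. The power loss is therefore conditional, and it is small for large effects.
- **The aim speaks of changes.** If change scores are used, baseline is partly handled, and the bias in the table is at most about 0.05 SD. It is reduced, not removed.
- **No preferred null.** A reader might infer that a finding of no mediation by body composition would suit the investigators. Section 2 points the other way: it sets weight loss aside and favours body composition as the relevant pathway. With a true effect of 0 and positive baseline correlation, leaving out the baselines pushes towards finding mediation.
- **Visit order is partly preference.** Relating the 6-month mediator to the 12-month outcome uses time order, but it says nothing about the 6-month outcome. It also leaves the 6-month outcome free to drive both variables.
- **The aim is exploratory.** That limits the consequence, but it does not justify a model that omits baselines the trial already measures.

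**Conclusion.** The point holds as one of bias and incomplete specification. The stated model is closed at three variables and omits the baseline mediator and baseline outcome, so the indirect effect is exposed to confounding on the path that randomisation does not protect. With a true value of 0, the spurious effect is about 0.03 to 0.13 SD on follow-up values and 0.01 to 0.05 SD on change scores. Adjustment for both baselines removes it in these calculations. That is so because the baselines are the only confounders simulated; in the trial, unmeasured causes of both fat change and glucose change could remain.

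The sizes rest on assumed correlations of 0.2 to 0.4, stabilities of 0.5 to 0.8 and a group effect of 0.5 SD on the mediator, none of which is in the documents. The mediator-to-outcome path, the visits and the interval method need to be stated. The loss of roughly 10 to 20 power points applies only if a normal-theory test is meant and the paths are moderate. The primary analysis is not affected.

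**What to change.** In Section 16, Specific Aim 3:

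1. Write two equations. Mediator on group, baseline mediator and baseline outcome. Outcome on group, mediator, baseline mediator and baseline outcome. The indirect effect is the group coefficient from the first times the mediator coefficient from the second; the direct effect is the group coefficient from the second.
2. Replace the three-variable limit accordingly, and say whether follow-up values or changes are used.
3. State the visits for mediator and outcome. The 6-month mediator with the 12-month outcome is one option.
4. Give the indirect effect an asymmetric 95% interval, by bootstrap or from the distribution of the product.
5. State that the mediator-to-outcome path is not randomised and that the aim stays exploratory.

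The cost is a few sentences. The baseline DXA and glucose tolerance measurements are already collected, so no visits, participants or assays are added.

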Children are presented with the results of their glucose tolerance test in the first class as a way to frame the discussion around diabetes and health. Each session begins with a low fat, high fiber snack and recipe (role modeling), acknowledgment and reinforcement of healthy behavior changes and progress towards individual goals (emotional and instrumental support), problem-solving challenges, and an outline of the session's goals. Children are incentivized through a point system for attendance, completing out of class 'assignments' such as helping to prepare a healthy meal for the family (enacting behaviors), participating in group discussions, and making progress towards their individual health goals. Parents and children work with other families during classes and are encouraged to do so outside of class in order to build a support network that extends beyond the program. Classes are delivered using a tiered approach where the first 16-sessions are delivered weekly while the last 4 session are spread over 8 weeks (total intervention period is 6-months). We have found that this delivery approach builds resiliency within families as they become less reliant on the health educators and more independent in achieving their health and behavior goals. Following the intervention period, children will return for post-intervention testing.

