**Intervention (Physical Activity):** The PA intervention includes structured and unstructured components. The structured PA curriculum is led by YMCA instructors and delivered 2 days/week to groups of 8-10 youth (both boys and girls) for 60-minutes each. Classes include aerobic and resistance exercises delivered in a progressive manner with the first 2-4 weeks focusing on motor skill acquisition, exercise confidence, developing a fitness base, and building camaraderie among participants. Aerobic exercises include group activity classes (e.g. spinning and cardio kick-boxing) with the goal of maintaining heart rates > 150 BPM. Real-time heart rate monitoring and rate of perceived exertion are used to monitor and document exercise intensity throughout the program. This exercise intensity was selected for the established effects on improving metabolic health in obese youth. Resistance exercise includes circuit training using age and size appropriate equipment and is incorporated because our previous studies suggest this form of exercise is both enjoyable and metabolically beneficial for obese youth. In addition to structured PA classes, youth are 'prescribed' an additional day of unstructured PA of at least 60-minutes with a family member or peer in the program. This allows for flexibility in pursuing preferred activities that can be done at the YMCA or elsewhere in the community in order to promote social support, role modeling, bonding among youth and families, and facilitate sustainability.

**Booster Sessions:** Three booster sessions (months 7, 8, and 9) following the completion of the intensive lifestyle period will be held to support the maintenance of healthy lifestyle behaviors, address any challenges encountered, and promote successes achieved. Post-intervention clinical measures will be returned to participants at the first session and changes in health status will be discussed in the context of maintaining healthy lifestyle behaviors.

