**BIOSCIENCE INSTRUCTIONS AND TEMPLATE**

| NUMBER   | DATE      | PAGE    |
|----------|-----------|---------|
| HRP-503b | 3/22/2022 | 8 of 13 |

Cost and Compensation: There is no cost to participate in this study. Participants will be reimbursed up to \$50 for their time and travel for each clinical testing visit and will receive a 12-month YMCA membership. In addition, participants will be able to earn incentives such as T-shirts, water bottles, and gift cards for attendance, participation, and responding to retention efforts.

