**Specific Aim 4:** To examine the cost effectiveness of the intervention, we will estimate the incremental cost-effectiveness ratio (ICER) of the intervention compared to UCC based on changes in 2-hour glucose. The cost effectiveness analyses will be conducted from the societal perspective using 2-hour glucose at 12 months, direct medical costs, and non-medical costs. Direct medical costs include: personnel, intervention materials, MD and RD visits, lab tests, and procedures. The non-medical costs will be participant time for travel, productivity loss, and commercial services for PA and nutrition. Base case and sensitivity analyses will be conducted using TreeAge software. The base case analysis model will use 6-month intervention costs and glucose tolerance at 12-months. ICERs will be calculated by dividing incremental costs by incremental effectiveness (change in 2-hour glucose). The results will indicate whether improved glucose tolerance leads to cost savings. Costs collected throughout the study will be inflated based on the published inflation rates in US dollars at the end of the study.

Confidentiality will be protected through the use of study identification numbers that will be kept separate from personal identifiers. A secure, password protected database will serve as the link between study IDs and source documents which will be kept in separate double-locked file cabinets at Arizona State University in the Southwest Interdisciplinary Research Center (SIRC) data storage in the UCENT building room 700. With the exception of the consent, contact information sheet, eligibility, clearance forms, and lab reports used in the context of the lifestyle class, all study materials will identify participants solely by the assigned code numbers. Blood specimens will be stored with ID numbers in the PI's freezer in ABC-1 rm 259-A. Members of the research team will have access to de-identified data. ID numbers will be used and de-identified data will be entered into a password protected computerized database after baseline testing and confirmation of eligibility. Data will be stored for 7 years; paper documents will be shredded and electronic files will be erased.

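### The Aim 4 base case sets 6-month intervention costs against a 12-month effect, so it omits the month 7–9 booster sessions and makes the ICER too low

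*Supplement*

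**What the plan says.** Section 16, Specific Aim 4, sets the perspective and outcome: "The cost effectiveness analyses will be conducted from the societal perspective using 2-hour glucose at 12 months, direct medical costs, and non-medical costs". The non-medical costs are listed as "participant time for travel, productivity loss, and commercial services for PA and nutrition". The headline analysis is then fixed: "The base case analysis model will use 6-month intervention costs and glucose tolerance at 12-months". The ratio is incremental cost over incremental change in 2-hour glucose. The paragraph adds: "The results will indicate whether improved glucose tolerance leads to cost savings". Sensitivity analyses are planned, but their content is not described. The plan also refers to costs gathered over the whole study, in the context of adjusting them for inflation.

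Section 8 describes what is delivered and when. The nutrition curriculum has 20 sessions, of which "the last 4 session are spread over 8 weeks (total intervention period is 6-months". After that, "Three booster sessions (months 7, 8, and 9) following the completion of the intensive lifestyle period will be held". Usual-care participants see the endocrinologist and the dietitian at baseline and 6 months. Monthly retention contacts go to everyone. Under Cost and Compensation, participants "will receive a 12-month YMCA membership". Under Usual Care Control, control youth are offered a one-year membership once they have finished the study.

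**The concern.** An ICER should charge the resources used to obtain the effect it counts. Here the effect is read at month 12, while the programme is costed for six months. In between, the intervention arm receives boosters whose stated purpose is maintenance, which is what a 12-month outcome picks up. Usual care has no matching programme activity in months 7–12. The omitted delivery cost therefore falls on one arm, and the error favours the intervention. Enrolling more participants would not remove it.

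The savings sentence is a second fault in the same paragraph. Dollars per mg/dl tie a glucose change to no later cost. A saving caused by better glucose tolerance at 12 months also cannot show up in costs that closed at month 6. Cost-effectiveness is one of the four specific aims and the base case is its main result, so a favourable ratio or a savings statement could be quoted without the qualification it needs.

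**Working it through.** **Inputs from the protocol.** Education sessions: 20 (Section 8). Structured exercise classes: 2 per week (Section 8). Total intervention sessions: 72 (Section 9). Boosters: 3, in months 7–9 (Section 8). No unit cost, total cost or expected ICER is given.

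**Step 1: are the boosters inside the 6-month programme?** The only volume figure to reproduce is the 72 sessions.
- 20 + 2 × 26 weeks = 72, which matches.
- 20 + 2 × 24 weeks = 68, which does not. Adding the boosters gives 71, still not 72.
- Adding the boosters to the 26-week count gives 75.

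The stated total is met by six months of education and exercise without the boosters. The match supports this reading but is not the only evidence: Section 8 places the boosters after the intensive period ends and calls the total intervention period six months.

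**Step 2: effect on the ICER.** Let C be the 6-month intervention cost, B the booster cost and U the usual-care cost. The 12-month effect is the same in both versions and cancels:

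ICER with boosters ÷ base-case ICER = (C + B − U) ÷ (C − U)

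With C − U > 0 and a positive benefit, any B > 0 makes this ratio exceed 1.

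**Step 3: size under stated assumptions.** Write b = B/C and u = U/C.

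| Assumption on booster cost | b | Ratio, u = 0 | Ratio, u = 0.25 |
|---|---|---|---|
| Each booster costs the same as an average session | 3/72 = 0.042 | 1.042 | (1.042 − 0.25)/0.75 = 1.056 |
| Education sessions carry all the cost, and a booster costs the same as one of them | 3/20 = 0.15 | 1.15 | (1.15 − 0.25)/0.75 = 1.20 |

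With usual-care cost ignored, the ICER rises by about 4% to 15%. Equivalently, the base case understates it by 1 − 1/1.042 = 4% to 1 − 1/1.15 = 13%. If usual care is assumed to cost a quarter of the 6-month intervention, the rise is 5.6% to 20%.

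**Step 4: what cannot be sized.** Membership cost in months 7–12 would add to the numerator if it falls there, but the protocol does not say when the membership starts, which arm receives it under that sentence, or how the fee is booked. Travel, productivity and commercial-service costs in months 7–12 arise in both arms, and their difference could go either way.

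**The case against.** The strongest reply is that the cost phrase may simply mean the cost of delivering the six-month programme, with household costs still gathered for the full year. That is a fair reading, and the mention of costs collected throughout the study gives it some support. It means one cannot say that every cost in both arms is cut off at month 6. It does not bring the boosters in, because on either reading they come after the six-month programme. The sensitivity analyses might cover the gap, but their content is not given, and they would not change the base case.

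Three stronger readings are tempting and are not supported.
- A reader might infer that half of the YMCA membership (6 of 12 months) is left out. That requires a start at baseline, provision to the intervention arm only and month-by-month costing. None of these is stated, and a fee paid at enrolment could sit wholly inside the six-month costs.
- A reader might take the boosters as 3 of 23 education-type sessions (13%), or assume that months 7–12 add 10–20% to incremental cost and so an understatement of 9–17%. The first leaves out all the exercise classes, and the second has no source in the protocol.
- A reader might conclude that cost-effectiveness is overstated across all societal costs. The direction is firm only for delivery cost.

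On savings, it is fair to say that a negative incremental cost would show a within-trial saving, and the numerator could reveal that. What fails is attributing a saving to improved glucose tolerance.

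**Conclusion.** The concern holds for delivery cost. As written, the Aim 4 base case omits three intervention-arm booster sessions that are meant to sustain the effect it counts, so the ICER is too low if incremental cost and benefit are both positive. On the assumptions shown, with usual-care cost ignored, correcting this raises the ICER by about 4% to 15%. The true size cannot be found from the protocol, and the boosters alone may be a small share. Any membership cost after month 6 would add to the understatement. Household and commercial-service costs could move the ratio either way.

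The savings sentence does not follow from the planned ratio, however large or small the booster cost is.

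Severity is moderate. The point changes the main result of the last of four aims and leaves the Aim 1 analysis of 2-hour glucose untouched.

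**What to change.** Define the base case over 0–12 months for costs and effect in both arms. Include the boosters, any membership cost falling in that period, usual-care visits and the non-medical costs already listed. State the arm, start date and booking of the membership. Report 6-month costs with the 6-month effect as a sensitivity analysis.

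Replace the savings sentence with a commitment to report incremental cost per mg/dl of 2-hour glucose and its uncertainty, and to claim a within-trial saving only if the 12-month incremental total cost is below zero.

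The price is a change of wording, modest extra cost capture for months 7–12 (the plan already refers to collecting costs throughout the study) and an ICER that will probably look less favourable.

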**Specific Aim 2:** Compare intervention effects to usual care on changes in QoL.

**Specific Aim 3:** Explore the mediating effects of changes in body composition on changes in T2D risk markers.

**Specific Aim 4:** Estimate the incremental cost effectiveness for improving glucose tolerance between groups.

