**Health Screening and Metabolic Phenotyping:** Potential participants will arrive at the ASU Clinical Research Unit at ~8:00 AM after an overnight fast for initial screening including a brief health history, height and weight measurement to calculate BMI percentile, and a standard 75g OGTT for fasting and 2-hour glucose (assessed by SonoraQuest Laboratories). Participants meeting inclusion criteria (described above) will return within 4 weeks of the screening OGTT for baseline testing to include in-depth medical and family history (including in utero exposure to gestational diabetes) and a brief physical exam. Height, weight, and waist circumference will be measured to the nearest 0.1cm, 0.1 kg, 0.1cm, respectively. Sitting blood pressure will be measured in triplicate using an appropriately-sized cuff on the right arm after 5 min of rest. A fasting lipid panel will be collected to measure cholesterol (Total, HDL, and LDL), triglycerides, and HbA1c. These assessments follow current recommendations for screening in obese youth, will be used in the curriculum to discuss the health risks of obesity, and are an important and meaningful benefit to families.

**Glucose Tolerance and Insulin Sensitivity (Aim 1):** Glucose tolerance and insulin sensitivity will be assessed by a 75 gram OGTT with multiple blood sampling for insulin glucose. Blood samples will be collected from an in-dwelling catheter at -15', -5', 30', 60', 90' and 120' for measurement of plasma glucose (glucose oxidase, YSI INC., Yellow Springs, OH) and insulin (ELISA, ALPCO Diagnostics, Windham, NH). At time 0', participants will ingest 75 grams of glucose in solution. Improvements in glucose tolerance will be assessed by decreases in 2-hour glucose levels (primary outcome) while changes in insulin sensitivity will be estimated by the whole-body insulin sensitivity index. For the purposes of this study, glycemic status will be defined as "Normal" (fasting glucose <100 mg/dl and 2-hr glucose <120 mg/dl), "Prediabetic" (fasting glucose ≥100 mg/dl or 2-hr glucose ≥120 mg/dl), or "Diabetic" (fasting glucose ≥126 mg/dl or 2-hr glucose ≥200 mg/dl). **NOTE:** Youth identified as "diabetic" at any point in the study will be referred for follow-up care and given the option to continue with the study with clearance from their physician.

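### The Aim 4 ICER should use the baseline-adjusted 12-month effect on 2-hour glucose already planned for Aim 1, with its direction stated

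*Supplement*

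**What the plan says.** Section 16, Specific Aim 4, describes the effect side of the ICER in several ways:

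- The comparison is of the intervention "compared to UCC based on changes in 2-hour glucose".
- The analysis is done "using 2-hour glucose at 12 months, direct medical costs, and non-medical costs".
- On the base case: "The base case analysis model will use 6-month intervention costs and glucose tolerance at 12-months".
- On the ratio: "ICERs will be calculated by dividing incremental costs by incremental effectiveness (change in 2-hour glucose".

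Three other places bear on how to read this. Section 8 sets the direction of benefit: "Improvements in glucose tolerance will be assessed by decreases in 2-hour glucose levels (primary outcome". Section 2 gives the aim as: "Estimate the incremental cost effectiveness for improving glucose tolerance between groups". Section 16, Specific Aim 1, gives the efficacy estimator: "ANCOVA models will use pretest measures as a covariate and the experimental groups (i.e., intervention vs. UCC) for comparisons", with 6 and 12 months analysed separately. Specific Aim 2 says that it reuses the Aim 1 models. Specific Aim 4 does not.

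**The concern.** The ICER denominator and the Aim 1 result describe the same thing: the effect of the intervention on 2-hour glucose at 12 months. Aim 1 adjusts it for baseline. Aim 4 calls it a change, and also a 12-month value, without saying whether or how baseline is handled. An analyst could use a difference in mean change, a difference in 12-month means or the ANCOVA difference, and could claim to follow the plan with any of them.

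Two things are at stake. The first is precision: the effect is the denominator of a ratio, so avoidable noise there carries straight into the ICER. The second is consistency: the efficacy and cost-effectiveness results could quote different effects for the same youth at the same visit, and the choice could be made after the data are seen.

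Direction is a smaller matter. Lower glucose is better, and the ratio sentence does not say which direction of change counts as positive. Aim 4 intends to draw a conclusion about cost savings, so a reader needs to know what the sign means.

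**Working it through.** **No stated figure to reproduce.** The documents give no ICER, incremental cost, glucose effect, SD or baseline-to-12-month correlation. The inputs below are therefore assumptions, apart from the planned total of 120 (Sections 2 and 5). The allocation ratio is not stated; 1:1 (60 per arm) is assumed, and it cancels from the variance ratios.

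**1. How the three estimators relate.** Let D0 and D12 be the intervention-minus-UCC differences in mean 2-hour glucose at baseline and 12 months, and let b be the within-group slope of the 12-month value on baseline.

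- Difference in mean change: D12 - D0
- Difference in 12-month means: D12
- ANCOVA: D12 - b x D0

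Randomisation makes D0 zero on average, so all three are unbiased. In any one trial D0 is not exactly zero, so they differ: change minus ANCOVA is -(1 - b) x D0, and 12-month mean minus ANCOVA is b x D0.

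**2. Precision.** With equal SDs at the two visits (so b is about r), the variances are proportional to 2(1 - r) for change, 1 for the 12-month mean and 1 - r^2 for ANCOVA. Hence change/ANCOVA = 2(1 - r)/(1 - r^2) = 2/(1 + r), and 12-month mean/ANCOVA = 1/(1 - r^2). Taking square roots gives the SE ratios. The effective sample size for change is 120 x (1 + r)/2.

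| assumed r | variance, change/ANCOVA | SE, change/ANCOVA | effective N of 120 | SE, 12-month mean/ANCOVA |
|---|---|---|---|---|
| 0.3 | 1.54 | 1.24 | 78 | 1.05 |
| 0.5 | 1.33 | 1.155 | 90 | 1.155 |
| 0.7 | 1.18 | 1.085 | 102 | 1.40 |
| 0.9 | 1.05 | 1.026 | 114 | 2.29 |

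A simulation with 60 per arm and 4,000 runs gave change/ANCOVA SE ratios of 1.25, 1.15 and 1.08 at r = 0.3, 0.5 and 0.7, in agreement with the formula. Neither unadjusted choice is safe across the range: change does worse at low r, and the 12-month mean does worse at high r.

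**3. Size of disagreement.** D0 has standard deviation SD x sqrt(2/60) = 0.183 SD. For an assumed SD of 25 mg/dl this is 4.6 mg/dl, which is also the typical gap between the change and 12-month-mean versions. The gap between change and ANCOVA is (1 - r) x 4.6: about 3.2 mg/dl at r = 0.3, 2.3 at 0.5 and 1.4 at 0.7.

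**4. Sign.** Assumed changes are -20 or 0 mg/dl in the intervention arm against -10 in UCC. Assumed incremental costs are +$2,000 or -$500.

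| intervention is | incremental cost | reduction (UCC minus intervention, in change) | ICER on reduction | ICER on follow-up minus baseline |
|---|---|---|---|---|
| dearer, better | 2000 | -10 - (-20) = +10 | +200 | -200 |
| dearer, worse | 2000 | -10 - 0 = -10 | -200 | +200 |
| cheaper, better | -500 | +10 | -50 | +50 |
| cheaper, worse | -500 | -10 | +50 | -50 |

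Coding changes only the sign. Under either coding, each sign is shared by two different situations, so the ratio alone does not identify the quadrant.

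**The case against.** Aim 4 names no estimator, so nothing in it requires an unadjusted one. Regressing change on group and baseline gives the same group coefficient as regressing the 12-month value on group and baseline. The ANCOVA effect is therefore compatible with the word change. The 12-month wording may simply give the time point, with change giving the quantity. The document is an IRB protocol with no separate analysis plan shown, Section 8 calls the cost-effectiveness work initial, and the precision loss is small if r is high.

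Much of this stands. The loss is conditional on an unadjusted reading, and the primary analysis is untouched. It does not remove the point. The protocol does give a formula for this ratio, a difference in mean change is the ordinary reading of it, and Aim 2 makes the link to the ANCOVA that Aim 4 leaves out.

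A reader might infer more in two respects.

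- **Reversed sign.** One might conclude that the plan prescribes a ratio in which a better but dearer programme comes out negative. That needs change to mean follow-up minus baseline. The phrase is a gloss on effectiveness, Section 8 defines improvement as a decrease, and Section 2 speaks of improving glucose tolerance. A sensible analyst would code reduction as positive. What is missing is a stated convention.
- **Bias from selecting on high glucose.** One might argue that change scores are biased because of the eligibility criterion. Over-correction of chance baseline imbalance arises whenever r is below 1, whatever the selection, and it averages to zero under randomisation.

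**Conclusion.** The point holds as a free improvement to a secondary aim. The ICER effect is not tied to the baseline-adjusted 12-month estimate already planned under Aim 1. Read as a simple difference in mean change, it has about 1.5, 1.3 or 1.2 times the ANCOVA variance at r = 0.3, 0.5 or 0.7, which is an SE larger by 24%, 15.5% or 8.5%. At r = 0.9 the SE penalty falls to 2.6%. These figures rest on an assumed r and equal SDs at the two visits. The mg/dl gaps also assume an SD of 25 and 60 per arm.

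The documents do not support a claim of bias, of a prescribed sign error or of any effect on the primary analysis. Nor do they give a basis for saying how likely Aims 1 and 4 are to disagree in sign.

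**What to change.** In Section 16, Specific Aim 4:

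1. Define incremental effectiveness as the baseline-adjusted between-group difference in 2-hour glucose at 12 months from the Aim 1 ANCOVA, expressed as a reduction: UCC minus intervention, positive = benefit.
2. Use this one quantity in the base case and the sensitivity analyses.
3. Aim 1 examines the main effect only if no baseline-by-group interaction is found, so state that, if one is found, the adjusted difference at the mean baseline is used.
4. Report incremental cost, incremental effect and the cost-effectiveness quadrant with the ICER. A rule that merely names the arm that is both cheaper and better would not do, because no such arm exists when the intervention is cheaper and less effective.

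The cost is a few sentences. The baseline measurement and the ANCOVA are already planned, and no further data are needed. The wording should be fixed before costs and outcomes are combined.
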